### EXCLUSION CRITERIA

1. History of any medical, psychological or other condition, or use of any medications, including over-the-counter products and hormonal therapies, which, in the opinion of the investigators, would either interfere with the study or potentially cause harm to the participant
2. Medical or psychological conditions that would impair their ability to participate reliably in the study or give informed consent
3. Pregnancy and/or breastfeeding

4. Without access at home to a telephone, or other factor likely to interfere with ability to participate reliably in the study
5. History of hypersensitivity to any of the components administered
6. Treatment with an investigational drug within the preceding 2 months
7. Those who have or intend to donate blood or blood products within three months before or following study completion
8. A history of major haematological, renal, thyroid or hepatic abnormalities or significant cardiovascular disease
9. A history of cancer

#### 4.3. WITHDRAWAL CRITERIA

If a participant loses capacity during the study, then they would be withdrawn from further participation in the study. However, any data or samples that we had already collected when they were able to give consent would be used in the study. We will seek their informed written consent for this at the screening visit. If consent is not given to this and the participant loses capacity, samples would be disposed of in accordance with the Human Tissue Authority's Code of Practice following completion of the study and not kept for use in future ethically approved research.

Any significant adverse effects will lead to withdrawal of the individual and any serious adverse effects will terminate the whole study.

It will be made clear to participants that they will be free to withdraw from the study at any time without providing any reason.

## 5. ADVERSE EVENTS

#### 5.1. DEFINITIONS

**Adverse Event (AE):** any untoward medical occurrence in a patient or clinical study subject.

**Serious Adverse Event (SAE):** any untoward medical occurrence or effect that:

- **Results in death**
- **Is life-threatening** – *refers to an event in which the subject was at risk of death at the time of the event; it does not refer to an event which hypothetically might have caused death if it were more severe*
- **Requires hospitalisation, or prolongation of existing inpatients' hospitalisation**
- **Results in persistent or significant disability or incapacity**
- **Is a congenital anomaly or birth defect**

Medical judgement should be exercised in deciding whether an AE is serious in other situations. Important AEs that are not immediately life-threatening or do not result in death or hospitalisation but may jeopardise the subject or may require intervention to prevent one of the other outcomes listed in the definition above, should also be considered serious.

## 5.2. REPORTING PROCEDURES

All adverse events should be reported. Depending on the nature of the event the reporting procedures below should be followed. Any questions concerning adverse event reporting should be directed to the Chief Investigators in the first instance.

### 5.3.1 Non serious AEs

All such events, whether expected or not, should be recorded.

### 5.3.2 Serious AEs

An SAE form should be completed and emailed to the Chief Investigators within 24 hours. However, hospitalisations for elective treatment of a pre-existing condition do not need reporting as SAEs.

All SAEs should be reported to the Riverside Research Ethics Committee (studies in men) and the West London Research Ethics Committee (studies in women) where in the opinion of the Chief Investigators, the event was:

- 'related', ie resulted from the administration of any of the research procedures; and
- 'unexpected', ie an event that is not listed in the protocol as an expected occurrence

Reports of related and unexpected SAEs should be submitted within 15 days of the Chief Investigators becoming aware of the event, using the NRES SAE form for non-IMP studies. The Chief Investigators must also notify the Sponsor of all related and unexpected SAEs.

Local investigators should report any SAEs as required by their Local Research Ethics Committee, Sponsor and/or Research & Development Office.

## 6. ASSESSMENT AND FOLLOW-UP

No specific follow-up will be required.

Very rarely, abnormalities may be detected (including during the screening visit) that warrant further investigation. In this situation the result would be communicated first to the participant and then to the participant's GP, who will arrange the appropriate specialist referral. A significant abnormality (or change in eligibility) would lead to exclusion from further participation in the study.

The definition of the end of the study will be once the last participant has completed their final study visit and the data collection (which includes analysis of blood samples) is complete.

## **7. STATISTICS AND DATA ANALYSIS**

This will be the first study investigating the effects of intranasal kisspeptin administration on reproductive hormone release in humans. Our previous work in healthy volunteers demonstrates that intravenous kisspeptin increases serum LH (mean 10.2 IU/L and standard deviation 0.4 IU/L), compared with placebo administration (mean 2.0 IU/L, standard deviation 0.1 IU/L) (11), and we predict a similar response following intranasal administration. Therefore, using these data, with  $\alpha = 0.05$ , power = 0.8 and effect size = 0.997, we performed a power calculation resulting in a sample size of 10 participants per group (*Group A* and *Group B*). To allow for dropouts and exclusions (estimated to be around 20%), 12 participants per group (*Group A* and *Group B*) will be recruited. It should be noted that regarding patients with reproductive disorders (*Group C*), the sample size will depend upon the specific disorder. For instance, our previous work demonstrates that the gonadotropin response following kisspeptin administration is similar in patients with polycystic ovary syndrome versus healthy women but augmented in patients with hypothalamic amenorrhoea [unpublished data].

Hormone level data will be assessed for normality and appropriate statistical methods chosen. Continuous data will be reported as measures of central tendency and of spread (e.g., mean and standard error of the mean or median and interquartile range as appropriate). For all study groups, time profiles of hormone levels during the 4-hour study period will be compared using two-way ANOVA with Bonferroni multiple comparison test [if the data is parametric], or Kruskal-Wallis test [if the data is non-parametric]. Mean responses (e.g., maximal increase and area under curve) will be compared using one-way ANOVA with Bonferroni multiple comparison test (*Group A*) and paired t-tests (*Group B* and *Group C*) [if the data is parametric] or Kruskal-Wallis test (*Group A*) and Wilcoxon signed-rank test (*Group B* and *Group C*) [if the data is non-parametric].  $P < 0.05$  will be considered statistically significant.

Data and all appropriate documentation will be stored for a minimum of 10 years after the completion of the study, including the follow-up period.

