## 2. STUDY OBJECTIVES

### Primary Outcome:

Change in serum LH following intranasal administration of kisspeptin compared to placebo. Blood samples will be taken at baseline (pre-administration) and every 15 minutes for 4 hours.

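### A normality check on small groups picks the primary LH test, and in Group A both tests it can pick ignore the crossover pairing

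*Protocol*

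**What the plan says.** The primary outcome (Protocol, Section 2) is "Change in serum LH following intranasal administration of kisspeptin compared to placebo". Section 7 sets the rule for all hormone data: "Hormone level data will be assessed for normality and appropriate statistical methods chosen". It then names both branches.

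- **Time profiles, all groups:** "compared using two-way ANOVA with Bonferroni multiple comparison test [if the data is parametric], or Kruskal-Wallis test".
- **Summary responses (maximal increase, area under the curve):** one-way ANOVA with Bonferroni in Group A if parametric; otherwise the text runs "paired t-tests (*Group B* and *Group C*) [if the data is parametric] or Kruskal-Wallis test (*Group A*) and Wilcoxon signed-rank test" for Groups B and C.

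No normality test, threshold or tested quantity is named, and no transformed scale is offered. A p-value below 0.05 "will be considered statistically significant". Section 3 describes a crossover in which every participant attends all visits and is compared with himself or herself. Group A has five visits; Groups B and C have two. Planned sizes are 10 evaluable and 12 recruited in Groups A and B, and a minimum of 6 in Group C.

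**The concern.** There are two linked problems.

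1. **The data choose the test.** With 6 to 12 paired differences a normality check has little power, so repeats of the same trial would sometimes use a t-test and sometimes a rank test. These can disagree on whether the primary result is significant.
2. **The pairing is lost in Group A.** The parametric test named there is an ordinary one-way ANOVA, and its non-parametric partner is Kruskal-Wallis, a test for independent samples. Neither removes differences between men, which is what the crossover was chosen to do. For time profiles, Kruskal-Wallis has the same fault in every group. It also has a single factor, so it cannot address treatment by time.

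At stake are the clarity of the primary result and, in Group A, much of the power that the design provides.

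**Working it through.** **Plan's own figure.** Inputs from Section 7: alpha 0.05 (two-sided assumed), "power = 0.8 and effect size = 0.997", "resulting in a sample size of 10 participants per group". For a paired t-test the noncentrality is 0.997 × √n. At n = 10 it is 0.997 × 3.162 = 3.15 on 9 degrees of freedom, and the power is 0.801. At n = 9 it is 0.746. So 10 is reproduced. An unpaired t-test at the same standardised effect would need 17 per arm and has power 0.56 with 10. The stated size therefore rests on a within-participant comparison.

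**Floor of the rank test.** The smallest exact two-sided Wilcoxon signed-rank p is 2/2ⁿ.
- Six pairs: 2/64 = 0.031, so all six differences must have the same sign.
- Five pairs: 2/32 = 0.0625, so significance at 0.05 is impossible.

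**Chance in the choice (Groups B and C, simulated).** Assumptions: a Shapiro-Wilk test at 0.05 on the paired differences picks a t-test or exact Wilcoxon; LH is lognormal with between/within-person CVs from 0.3/0.3 to 1.0/0.5; the log-scale standardised difference is 0.997; 10,000 runs per setting.

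| n | Check rejects normality | Power, planned rule | Power, fixed log-scale paired t |
|---|---|---|---|
| 6 | 8–28% | 0.34–0.45 | 0.50–0.51 |
| 10 | 13–50% | 0.68–0.76 | 0.80 |
| 12 | 15–58% | 0.77–0.85 | 0.88–0.89 |

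The loss is about 3 to 12 points at n = 10 to 12 and, before rounding, 5 to 18 points at n = 6. The t-test and Wilcoxon disagree on significance in 18–23% of trials at n = 6 and 5–24% at n = 10 to 12. Type I error of the planned rule is 0.036 to 0.054.

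**Counter-case.** If the differences are normal and additive (standardised difference 0.997, assumed lognormal baseline), the order reverses. Planned rule against log-scale test: 0.50 vs 0.43 (n = 6), 0.80 vs 0.65 (n = 10), 0.88 vs 0.71 (n = 12).

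**At the plan's predicted response.** Section 7 reports "intravenous kisspeptin increases serum LH (mean 10.2 IU/L and standard deviation 0.4 IU/L), compared with placebo administration (mean 2.0 IU/L, standard deviation 0.1 IU/L" and predicts a similar response by the intranasal route. The ratio is 10.2/2.0 = 5.1. With lognormal LH both approaches reach about 1.00 at n = 10 and 12. At n = 6 the planned rule has 0.85 to 1.00 and the log-scale test at least 0.997.

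**Pairing in Group A (simulated, five visits, n = 12, lognormal).**

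| Assumed spread and largest ratio to placebo | One-way ANOVA | Kruskal-Wallis | Repeated-measures ANOVA, raw | Repeated-measures ANOVA, log |
|---|---|---|---|---|
| CV 0.5 between, 0.3 within; 1.4 | 0.04 | 0.03 | 0.53 | 0.66 |
| log-SD 0.5 between, 0.3 within; 1.5 | 0.07 | 0.07 | 0.69 | 0.83 |
| CV 0.5 between, 0.3 within; 2.0 | 0.62 | 0.72 | 0.995 | 1.00 |
| CV 0.3 between, 0.3 within; 2.0 | 0.96 | 0.97 | 0.999 | 1.00 |

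In the second row the Friedman test reaches 0.70. With no treatment effect the independent-samples tests reject almost never, and the within-participant tests reject in about 4 to 5% of trials. The independent-samples tests are therefore very conservative, not liberal. Log scale alone gains little in Group A: in the third row a log one-way ANOVA has 0.77, against 0.73 for the normality-driven choice between the two planned tests.

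**The case against.** - **The rule simulated is an assumption.** The Protocol names no normality test, and its assessment could be a plot. An SAP not shown may define it. This stands as to the exact percentages. But the Protocol itself fixes the switch and names the tests in both branches.
- **A reader might infer that the rule loses power as such and that LH must be logged.** The documents do not support this. They do not describe the shape of LH, and the order reverses for an additive normal response. The two quoted SDs give CVs of 0.1/2.0 = 5.0% and 0.4/10.2 = 3.9%. Two such points fit a multiplicative scale, but at CVs this small they cannot separate raw from log.
- **A reader might infer that the normality switch causes Group A to lose its pairing.** It does not: the parametric branch, as written, ignores pairing too. A repeated-measures one-way ANOVA may have been intended, but the text does not say so, and Kruskal-Wallis is the partner of the independent-samples version.
- **A reader might infer false-positive risk.** None appeared in the cases tried. The time-profile Kruskal-Wallis was not simulated, because the text does not say how samples over time would enter it.
- **The predicted effect is large.** At a 5.1-fold rise the choice of branch barely matters for n = 10 to 12. That stands. But the prediction comes from intravenous data, and the Protocol calls this the first intranasal study in humans.

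**Conclusion.** The point holds in two parts. First, the primary LH test is left to a normality check that is close to uninformative in groups this small, and the branch taken can decide significance. Group C is most exposed: with only six patients, one loss plus a failed check rules out p below 0.05 whatever the effect. Against a fixed log-scale test the power consequence runs from a loss of about 3 to 18 points (lognormal LH) to a gain of about 7 to 18 points (additive normal response), and is almost nil at n = 10 to 12 for the predicted 5.1-fold rise.

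Second, and larger, Group A is analysed as if its visits came from different men. Under the assumed spreads this cuts power from about 0.7 to 0.8 to about 0.07 for ratios up to 1.5. The loss shrinks for larger responses or smaller differences between men. All spreads, ratios and distribution shapes are assumptions, as the Protocol gives none that could replace them.

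A reader might also infer that the dose carried into Groups B and C is affected. As written, that choice rests on the greatest maximal LH increase in Group A, not on a significance test, so the finding does not extend to it.

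**What to change.** Replace the normality-driven choice in Section 7 with one pre-specified analysis, for example:

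> The primary LH summary is [one named quantity, such as log peak LH or log LH area under the curve]. It will be compared between kisspeptin and placebo within participants in every group: a repeated-measures or mixed model with a participant effect in Group A, and a paired analysis in Groups B and C. The scale is fixed in advance and does not depend on a normality test. Friedman (Group A) and Wilcoxon signed-rank (Groups B and C) tests are sensitivity analyses only.

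The maximal increase should not be the logged quantity, because under placebo it can be zero or negative. Kruskal-Wallis should also be removed as the option for time profiles.

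The cost is wording only: no further participants, visits or samples. If the log scale is chosen, effects are reported as ratios, values below the assay limit need a stated floor, and some power is lost if the response is truly additive (7 to 18 points in the counter-case above).

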### Study Visits

Study visits will take place at the Clinical Research Unit (Imperial College Healthcare NHS Trust) and all participants within each group will receive the same protocol during each study visit.

**Group A (Healthy Men):** Kisspeptin has not been administered via the intranasal route to humans and thus this part of the study will also determine the optimal dosing protocol for intranasal kisspeptin delivery. Participants will attend for five study visits each and will receive the following five interventions (on separate visits and in random order) via the intranasal route: 3.2, 6.4, 12.8, and 25.6 nmol/kg of kisspeptin-54, and 0.9% saline (placebo). After self-administration of kisspeptin-54 or placebo at timepoint 0 minutes, serum levels of LH, FSH, and testosterone will be measured every 15 minutes for 4 hours (**see Figure 1**).

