**Figure 3 – Protocol Schematic (Group C)**

[figure not shown]

For all groups: On arrival to the Clinical Research Unit and following a period of acclimatisation, an intravenous cannula will be inserted into one antecubital fossa (for blood sampling). Female participants will have their urine tested for  $\beta$ -hCG (pregnancy test) at each study visit to ensure that they are not pregnant. Next, participants will receive a standardised education session explaining the procedure of intranasal administration (to ensure good technique). Blood will then be sampled at timepoints -30, -15, and 0 minutes (pre-administration baseline), followed by intranasal administration of kisspeptin-54 or 0.9% saline (placebo).

Thereafter, serum levels of LH, FSH, and testosterone (*Group A*), or oestradiol and progesterone (*Group B* and *Group C*) will be measured every 15 minutes for 4 hours. Heart rate, blood pressure, and the presence of adverse symptoms will also be recorded every 15 minutes. At least two clinically trained investigators will be present throughout each study visit.

Participants, study visit investigators, and the data analysts will be blinded to the identity of kisspeptin or placebo. The order of study visits will be randomised by an independent investigator prior to recruitment of the first participant. The randomisation sequence will be held centrally at Imperial College London by the CI's ([name] and [name]) who are not involved in the study visits and data analysis.

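### The Bonferroni follow-up of the hormone time profiles is valid but dominated by Holm, and is noticeably conservative only if neighbouring 15-minute samples are very highly correlated

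*Protocol*

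**What the plan says.** Protocol section 7 sets the method for the profiles: "For all study groups, time profiles of hormone levels during the 4-hour study period will be compared using" "two-way ANOVA with Bonferroni multiple comparison test", with the alternative "or Kruskal-Wallis test [if the data is non-parametric"]. Bonferroni is named only in the parametric branch, so this point concerns that branch. The text gives neither the number of comparisons nor the error term for the follow-up.

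The sampling schedule comes from section 2, Primary Outcome: "Blood samples will be taken at baseline (pre-administration) and every 15 minutes for 4 hours". Section 3 adds that "Blood will then be sampled at timepoints -30, -15, and 0 minutes (pre-administration baseline"), so time 0 precedes dosing. In Group A the active treatments are "3.2, 6.4, 12.8, and 25.6 nmol/kg of kisspeptin-54", with saline as the fifth arm.

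Section 7 also plans tests of single-number responses: "Mean responses (e.g., maximal increase and area under curve) will be compared using one-way ANOVA with Bonferroni multiple comparison test" in Group A and "paired t-tests" in Groups B and C.

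**The concern.** Serial samples taken 15 minutes apart tend to be positively correlated. Bonferroni takes no account of this, and it also spends the same fraction of alpha on every test whatever the others show. If the family is every sampling time, each test in Groups B and C is judged at about 0.003, and each test in Group A at below 0.001. Meanwhile 10 participants per group were chosen for a single comparison at 0.05. A profile with no significant time point could then partly reflect the correction. What is at stake is the description of where along the 4 hours the treatments differ. Whether LH responds at all can be tested on the summary measures.

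**Working it through.** **Inputs.** Section 7: alpha 0.05, power 0.8, effect size 0.997, 10 per group (12 recruited). Section 3: at least 6 in Group C; five treatments in Group A. Section 2: baseline plus every 15 minutes for 4 hours. Assumed here: two-sided tests, per-time comparisons, and AR(1) correlation between the paired differences at neighbouring times. The protocol gives no correlation.

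**1. The plan's own figure.** A two-sided paired t-test with standardised difference 0.997 has noncentrality 0.997 × √n on n − 1 degrees of freedom. At n = 10 and alpha 0.05 its power is 0.801, and 10 is the smallest n that reaches 0.80. The stated sample size is therefore reproduced as one unadjusted comparison.

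**2. Size of the family.** 240/15 = 16 post-dose times, or 17 with time 0. Group A has 4 contrasts with placebo (4 × 16 = 64, 4 × 17 = 68) or 10 pairs (10 × 17 = 170).

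**3. Power per comparison with Bonferroni, separate paired t-tests, effect 0.997.**

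| Comparisons m | 0.05/m | n = 10 | n = 12 | n for 80% |
|---|---|---|---|---|
| 1 | 0.05 | 0.80 | 0.88 | 10 |
| 16 | 0.00313 | 0.30 | 0.43 | 19 |
| 17 | 0.00294 | 0.29 | 0.42 | 20 |
| 68 | 0.00074 | 0.13 | 0.22 | 24 |
| 170 | 0.00029 | 0.07 | 0.14 | 27 |

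With the Group C minimum of 6, m = 17 gives 0.08.

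**4. How much of the loss is due to correlation.** This was simulated with 17 tests, n = 10 and 20,000 runs. Bonferroni's critical t is 4.04 and its power 0.289.

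| Correlation | True familywise error, Bonferroni | Critical t allowing for correlation | Power with it | Gain |
|---|---|---|---|---|
| 0.7 | 0.043 | 3.94 | 0.31 | 0.02 |
| 0.8 | 0.039 | 3.86 | 0.33 | 0.04 |
| 0.9 | 0.029 | 3.66 | 0.38 | 0.09 |
| 0.95 | 0.023 | 3.42 | 0.45 | 0.16 |

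The total fall is 0.80 − 0.29 = 0.51. Ignoring correlation accounts for 0.02 of it at 0.7 and 0.16 at 0.95. The rest is the price of testing 17 times.

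**5. Methods compared at equal multiplicity.** Simulated with 16 post-dose times, n = 10 and effect 0.997 at the first 6 times. Power per active time is about 0.29 with Bonferroni and 0.31 to 0.32 with Holm. With step-down max-T it is 0.32, 0.42 and 0.46 at correlations 0.7, 0.9 and 0.95.

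**6. Dependence on the error term.** Steps 3 to 5 use 9 degrees of freedom per test. A follow-up to an ANOVA commonly uses a pooled error instead. With 17 times:
- Variance of the paired differences pooled over times, 17 × 9 = 153 degrees of freedom, critical t about 3.02: power about 0.55 to 0.57, familywise error about 0.04 to 0.05. The simulation gave every time the same variance.
- Participant-by-time residual, 16 × 9 = 144 degrees of freedom: familywise error about 0.12 to 0.13 at correlation 0.7, rising to 0.46 to 0.48 at 0.95.

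**7. Smallest attainable max-T p-value.** With n sign flips the two-sided minimum is 2/2^n: 2/64 = 0.031 for 6 patients, but 2/32 = 0.0625 for 5.

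**The case against.** The strongest case against is that Bonferroni is a legitimate correction, and that the protocol never says it runs over every sampling time or that time 0 is in the family. Family definition is commonly left to a statistical analysis plan, which may exist and is not shown. That stands: the counts are an inference, and the undefined family is not itself the criticism.

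A reader might infer that Bonferroni wastes most of the power because the samples are strongly correlated. The documents do not support this. They give no correlation, and step 4 shows that the number of tests causes most of the loss.

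A reader might also infer that the LH conclusion is at risk. It need not be. Section 7 tests area under the curve and maximal increase without a time-point penalty, and no stated objective concerns the time of onset.

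The power figures are not for a pooled-error follow-up. Step 6 shows that such a follow-up could have higher power or could inflate the error rate, and the protocol does not say which applies. The protocol also does not state that 0.997 holds at each time. The LH means and SDs printed beside it imply about (10.2 − 2.0)/√(0.4² + 0.1²) = 8.2/0.41 ≈ 20 at zero correlation, and at that size any of these corrections would have power near 1.

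These points limit the size of the claim. They do not touch the ordering: for any given set of p-values, Holm rejects everything Bonferroni rejects and sometimes more, at the same familywise error and under any dependence.

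**Conclusion.** This is a low-cost improvement to the analysis, not an error. The protocol itself fixes Bonferroni for the parametric time profiles, and a uniformly better choice exists. On per-time paired t-tests with n = 10 and effect 0.997 at 6 of 16 times, Holm adds 2 to 3 points of power per active time. Step-down max-T adds about 3 points at correlation 0.7 and about 13 to 17 at 0.9 to 0.95. The conservatism of Bonferroni is small at 0.7 and matters only from about 0.9.

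These sizes rest on the per-time reading, the assumed correlations, the planning effect applied at each time, and separate error estimates at each time. Had the participant-by-time residual been used, the more serious fault would be inflated error. Within-participant paired tests at each time avoid it.

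**What to change.** In section 7, or in the statistical analysis plan if one exists:
- Limit the profile follow-up to post-dose times and dose-versus-placebo contrasts: 16 comparisons in Groups B and C, 64 in Group A. Time 0 precedes dosing and can show no drug effect.
- Make each comparison a within-participant paired test at that time.
- In Group A adjust by Holm. Jointly relabelling five treatments tests only the global null, so max-T is not advised for individual dose contrasts there.
- In Groups B and C adjust by step-down max-T with sign flips of the paired differences, or by Holm. Name one in advance. If max-T is named, state that Holm applies in Group C when fewer than 6 patients remain.

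The cost is a few sentences and a few lines of code. Simultaneous confidence intervals become less simple than with Bonferroni. If the spread of the paired differences truly were equal at all times, separate error estimates would give up the extra power of a pooled variance (step 6); in return, the result does not depend on that assumption.

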## 3. STUDY DESIGN

This is a randomised, double-blind, placebo-controlled, crossover study investigating the effects of intranasal kisspeptin administration on reproductive hormone release in healthy volunteers (men and women) and patients with reproductive disorders. The cross-over design has been chosen as it is the most rigorous method to determine a treatment effect, by minimising the effect of confounding variables. Each participant will be required to attend all study visits, hence serving as their own control.

**The study will recruit three groups of participants.** *Group A* will consist of healthy men with normal reproductive function and will also determine the optimal dose for intranasal kisspeptin administration. *Group B* will consist of healthy (ovulatory) women with normal reproductive function. *Group C* will consist of female patients with reduced reproductive function, such as HA. The groups will not be recruited in parallel, as the results from *Group A* will determine the optimal dosing for *Groups B* and *Groups C*.

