**Figure 1 – Protocol Schematic (Group A)**

[figure not shown]

**Group B (Healthy Women):** Participants will attend for two study visits each, receiving kisspeptin-54 and 0.9% saline (placebo) (on separate visits and in random order) via the intranasal route. The dose of kisspeptin-54 will be determined based on the results of Group A, i.e., the dose of kisspeptin-54 which elicits the greatest maximal increase in serum LH in healthy men. After self-administration of kisspeptin-54 or placebo at timepoint 0 minutes, serum levels of LH, FSH, oestradiol, and progesterone will be measured every 15 minutes for 4 hours (**see Figure 2**).

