**Figure 2 – Protocol Schematic (Group B)**

[figure not shown]

**Group C (Female patients with Reproductive Disorders):** Patients will attend for two study visits each, receiving kisspeptin-54 and 0.9% saline (placebo) (on separate visits and in

random order) via the intranasal route. The dose of kisspeptin-54 will be determined based on the results of *Group A* (described above) and will be the same dose examined in *Group B*. After self-administration of kisspeptin-54 or placebo at timepoint 0 minutes, serum levels of LH, FSH, oestradiol, and progesterone will be measured every 15 minutes for 4 hours (**see Figure 3**).

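### Group A responses and all hormone time profiles are assigned independent-sample tests, although every participant receives every treatment

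*Protocol*

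**What the plan says.** Protocol section 3 (Study Design) gives the reason for the crossover: "Each participant will be required to attend all study visits, hence serving as their own control". Under Study Visits, Group A is described thus: "Participants will attend for five study visits each and will receive the following five interventions" (four doses and placebo). For Group B: "Participants will attend for two study visits each, receiving kisspeptin-54 and 0.9% saline (placebo"). Group C has the same two-visit scheme. After dosing, hormones "will be measured every 15 minutes for 4 hours".

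Section 7 (Statistics and Data Analysis) then fixes the tests:

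- **Time profiles, all groups:** they "will be compared using two-way ANOVA with Bonferroni multiple comparison test [if the data is parametric], or Kruskal-Wallis test [if the data is non-parametric"].
- **Group A summary responses:** "Mean responses (e.g., maximal increase and area under curve) will be compared using one-way ANOVA with Bonferroni multiple comparison test", or Kruskal-Wallis if non-parametric.
- **Group B and C summary responses:** paired t-test, or Wilcoxon signed-rank if non-parametric.

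No participant factor, repeated-measures form, mixed model or Friedman test is named anywhere in the Protocol.

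**The concern.** One-way ANOVA and Kruskal-Wallis treat the five visits of one man as five different men. The differences between men that the crossover was meant to remove stay in the error term. Two-way ANOVA on treatment and time, without a participant or visit term, also counts each of the 16 post-dose samples of a visit as a separate observation. Kruskal-Wallis on pooled samples does the same and cannot express a treatment-by-time effect.

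The two faults act differently. On one summary value per visit, the test is too conservative and loses power. On serial samples, the p-value for the treatment effect is misstated, usually towards false positives. Change in serum LH is the primary outcome, so these tests carry the main claim of the study in Group A and the profile comparison in every group.

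**Working it through.** **1. The plan's own sample size.** Section 7 gives α = 0.05 (two-sided assumed), power 0.8, effect size 0.997 and n = 10.

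- Paired t-test, df = n − 1, noncentrality 0.997·√n: n = 9 gives 0.746 and n = 10 gives 0.801. The stated 10 is reproduced.
- One-sided paired test: 8 participants would suffice (0.813).
- Two-sample t-test, df = 2n − 2, noncentrality 0.997·√(n/2): 10 per arm gives 0.560; 17 per arm are needed (0.805).

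The plan is therefore sized on a two-sided paired comparison.

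**2. Group A summary responses.** The Protocol gives no within-man correlation ρ, so 0.3, 0.5 and 0.7 are assumed. One of the five treatments differs from the rest by δ, with paired effect dz = δ/(σ√(2(1−ρ))) = 0.997.

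With participant in the model, the noncentrality is n·(4/5)·δ²/(σ²(1−ρ)) = n·1.6·dz² = 10 × 1.6 × 0.994 = 15.9 on 4 and 36 df. Power is 0.86 whatever ρ is.

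In one-way ANOVA with no true effect, the treatment mean square has expectation σ²(1−ρ) but the error mean square has expectation σ². The F ratio therefore centres near 1 − ρ, that is 0.7, 0.5 and 0.3, instead of 1. Simulation (20,000 runs; 5,000 for rank tests), n = 10:

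| | ρ = 0.3 | ρ = 0.5 | ρ = 0.7 |
|---|---|---|---|
| Type I error, one-way ANOVA | 0.014 | 0.004 | 0.001 or less |
| Power, one-way ANOVA | 0.70 | 0.46 | 0.16 |
| Power, participant in model | 0.86 | 0.86 | 0.86 |
| Power, Kruskal-Wallis | 0.61 | 0.37 | 0.13 |
| Power, Friedman | 0.72 | 0.73 | 0.72 |

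With all 12 men, one-way ANOVA has about 0.81, 0.58 and 0.22, against 0.93. At ρ = 0 the two ANOVAs agree (0.88 and 0.87), so the loss comes from ignoring the participant.

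**3. Time profiles with no true effect.** Every 15 minutes for 4 hours gives 240/15 = 16 post-dose samples. Take change from one pre-dose sample, with independent sampling noise of variance v.

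- Expected treatment mean square: 16 × (v/16 + v) = 17v.
- Expected error mean square: 2v.
- F is inflated by 17/2 = 8.5.
- Two visits (n = 12): P(χ²₁ > 3.87/8.5) = 0.50.
- Five visits (n = 12): P(χ²₄ > 4 × 2.38/8.5) = 0.89.

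Simulations over a range of assumed variance components and serial correlation give 0.49 to 0.55 (two visits, n = 12), 0.48 to 0.53 (two visits, n = 6) and 0.88 to 0.91 (five visits, n = 12). Pooled Kruskal-Wallis gives 0.47 to 0.90 across the same settings.

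The baseline definition matters. If the mean of the three pre-dose samples (−30, −15 and 0 minutes) is subtracted and the noise is independent, the ratio is 16(v/16 + v/3)/(4v/3) = 6.33/1.33 = 4.75, and the rates become 0.37 and 0.73.

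On raw levels the treatment main-effect rate runs from 0.001 to 0.77. It is lowest when differences between participants dominate and there is little visit-to-visit variation or serial correlation. The treatment-by-time test is conservative throughout (0.007 or less). A within-participant analysis of the per-visit mean holds 0.04 to 0.06 in every setting.

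**The case against.** The strongest reply is that one-way and two-way ANOVA are often written loosely for their repeated-measures forms. The own-control rationale, the paired tests for Groups B and C and a sample size that reproduces only with pairing all point to that intent. This is a fair reading of intent, and it is why the parametric part is an error of what is written, not proof of what would be run. It does not rescue the plan. The same sentence marks pairing explicitly for Groups B and C and not for A, and the Kruskal-Wallis fallback is an independent-sample test on any reading.

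The power figures also depend on assumptions. Holding dz at 0.997 shrinks the raw effect as ρ rises, and at ρ = 0.3 the loss is moderate (0.70 against 0.86).

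A reader might infer more than the Protocol supports:

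- **That the dose carried to Groups B and C would be wrong.** Section 3 ranks doses by greatest maximal LH increase, not by a p-value. With complete data the dose means are the same under either ANOVA.
- **That the baseline is ignored.** The primary outcome is change in LH, maximal increase is a named summary, and section 3 defines the baseline samples: "Blood will then be sampled at timepoints -30, -15, and 0 minutes (pre-administration baseline"). Covariate adjustment is a preference.
- **That every time-profile test inflates false positives.** The inflation concerns the treatment main effect, and on raw levels it can reverse.
- **That a missing period term is an error.** Such detail may sit in a statistical analysis plan.

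**Conclusion.** The concern holds. As written, section 7 assigns independent-sample tests to within-participant data in two places: Group A summary responses, and time profiles in all groups. Kruskal-Wallis is wrong in both without qualification. The ANOVAs are wrong unless repeated-measures forms are meant, which the text does not state. The Group B and C summary tests are correctly paired.

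That the stated n needs a paired test rests only on the Protocol's own figures and a two-sided α. The size of the damage rests on a within-man correlation, variance components and a baseline definition that the Protocol does not give. Group A loses between about 0.16 and 0.70 of power over correlations 0.3 to 0.7. The direction of error in the time profiles depends on the scale analysed and on which effect is tested. Because the tests of the primary outcome do not match the design, this should be corrected before analysis.

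**What to change.** Amend section 7 as follows.

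- **Group A summary responses:** repeated-measures ANOVA or a linear mixed model with a participant term; visit number may be added. Rank fallback: Friedman, with paired Bonferroni-adjusted post-hoc comparisons.
- **Time profiles, all groups:** a repeated-measures or mixed model with participant, treatment, time and treatment-by-time, allowing for correlation within a visit. Rank fallback: paired tests on per-visit summaries (Friedman in Group A, Wilcoxon signed-rank in Groups B and C).
- **Kruskal-Wallis:** delete throughout.
- **Group B and C summary responses:** keep the paired t-test and Wilcoxon signed-rank test.

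The cost is protocol wording and slightly more analysis work, with no new participants, visits or samples. A log scale, a baseline covariate and balanced treatment sequences are optional refinements and not needed to correct this error.
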